#### Goal 3—To Quantitatively Test Attitudes Toward Aging Among the Young Adult Volunteers

The objectives are to (1) offer opportunities for trained young adult volunteers to engage with older adults in the 10-session intervention and (2) test changes in their attitudes toward aging after the intervention using surveys. Hypotheses include the following: (1) young adult volunteers in the intervention group will have more positive attitudes toward aging after the intervention compared with that before the intervention and (2) young adult volunteers in the intervention group will have more positive attitude toward aging after the intervention compared with those in the control group.

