## Methods

### Study Design

The proposed project will conduct a randomized controlled trial to assess the effects of the intergenerational reminiscence approach with DST on the social and emotional well-being of older adults with ADRD. An explanatory sequential mixed methods design [39] will be used, which first involves collecting quantitative data and analyzing the data to identify subsamples of participants who report the greatest and least changes and then conducting qualitative interview with these subsamples. Half (46/92, 50%) of the dyad sample will receive the reminiscence DST intervention, and the other half (46/92, 50%) of the sample will receive a regular social visit from young adult volunteers without the intervention. Dyads will be randomly assigned to either the intervention or control group after baseline screening of all participants and, subsequently, randomly matched within each group. To further prevent selection bias, statistical techniques such as covariate-adjusted linear mixed models will be used to adjust for covariate imbalance during data analysis.

A total of 92 dyads are required to test the effectiveness of the intervention in this proposed study (refer to power analysis in the *Sample and Recruitment Plan* section). We will recruit participants on a rolling basis until we recruit 92 dyads. At least one-fourth (23/92, 25%) of the total sample of older adults and young adult volunteers will be recruited before they are randomly matched. Upon signing the consent form, participants will be given the chance to engage in the study. They will be provided with guidance throughout the informed consent process and will subsequently undergo a baseline survey in which all measures will be collected blind to group conditions.

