### Sampling and Recruitment Plan

Power analyses performed using G*Power 3.1.9 indicated that a total of 92 dyads (or 184 participants) are required to address our study objectives using a linear mixed model. This sample size estimate was based on a small effect size *(f*=0.22), a significance level of α=.05, β of .20, anticipated *r* over time of 0.30, and 5% attrition rate based on the findings of Chung [25], for 2-tailed tests.

Participants in this study will be community-dwelling older adults and undergraduate and graduate students (ie, young adult volunteers) enrolled at UTA. The eligibility criteria of the older adult participants include individuals who (1) are aged ≥65 years; (2) have cognitive impairment measured by the Ascertain Dementia 8 (AD8) [41]; (3) have decisional capacity as measured by the University of California, San Diego Brief Assessment of Capacity to Consent (UBACC) [42]; (4) are not participating in any other research protocol currently; and (5) can speak and understand English. The exclusion criteria for older adults are (1) participating in another trial, (2) having health issues that prevent them from participating in the study for 3 months, and (3) inability to commit to being available for the full 10 weeks of the intervention.

The older adult participants will be recruited through Tarrant County Meals On Wheels (MOW), which is a partner agency of the Area Agency on Aging of Tarrant County. Eligibility criteria to enroll in Tarrant County MOW is that a person must be homebound and have no one to help them on a regular basis. The Area Agency on Aging is very committed to expanding services and supports to people with ADRD, as many MOW clients with ADRD are living alone in Tarrant County. Moreover, studies suggest the need for additional research in the area of loneliness among clients using MOW [43]. Participant recruitment will begin with case managers and other MOW staff using their client database system to search for clients with ADRD who meet the study criteria. Next, case managers will contact potential study participants and then ask for permission to share their telephone number with a member of the UTA research team. The principal investigators (PIs) and graduate research assistants (GRAs) will follow-up with all the potential participants provided by MOW.

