For quantitative data analyses, descriptive analyses will first be conducted to provide the overall means and frequencies of key outcome variables for both older and young participants in the intervention and control groups. Fisher exact tests, Pearson chi-square tests, and independent samples *t* tests (2-tailed) will be computed to test for group differences that may be attributable to participants, such as age, sex, education level, income, and health conditions. If the groups significantly differ on any of these variables, the variable will be incorporated into the following analyses as a covariate, thereby controlling for potential influences that the covariate may have on the dependent variables. Moreover, in the event that at the culmination of this study, our sample sizes are unequal in the treatment groups or our outcome data are nonnormal, we will follow through with appropriate statistical corrections where necessary. Covariate-adjusted linear mixed models for repeated measures will be performed to compare the intervention and control groups over time for the major outcomes of older adults and young adult volunteers. The covariate will be any significant variable yielded from the univariate analyses, and the dependent variable will be the scores before the intervention, in the middle of the intervention, at the end of the intervention, and at 3-month follow-up. In this study, 95% CIs will be computed for each adjusted mean difference. The study α will be set to .05, with no adjustments for multiple comparisons owing to the preliminary nature of this study and the increased risk of type-2 error as a result of α adjustment [70].

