Several different combinations of statistical results are possible. The results may indicate that the intervention and control groups significantly differ in outcomes among the older participants and the young adult volunteers. Another possibility is that differences may be discovered for one age group but not the others. Outcome measures may significantly change over time for none of the groups, some groups, or all groups. Another possibility is that the pattern of change over time for one group may not replicate in another group. This possibility, which would be identified via a significant interaction in linear mixed models, would require post hoc testing to investigate the nature of changes over time. In this case, groups will be isolated, and patterns of change will be identified via linear mixed models for repeated measures (with no between-participants factors). *For the qualitative data analysis*, the process will involve digitally recording and transcribing the qualitative interviews, followed by using conventional content analysis, as outlined by Hsieh and Shannon [71]. The research team, including LX and [name], along with the research assistants, will independently code the data, forming the foundation for an initial coding framework. Subsequently, the researchers will convene to compare and establish consensus on the coding outcomes. Pertinent excerpts from the transcripts will be extracted and reorganized based on thematic relevance. The constant comparison process, as described by Glaser and Strauss [72], will be used to explore similarities and differences among participants who did and those who did not benefit from the intervention, generating subthemes within the broad topics. This comparative approach will enhance consistency and broaden the dimensions and comprehensiveness of each code. Eventually, the codes will be synthesized or combined into overarching recurrent themes. During the analysis stage, themes, research notes, and field notes will be reviewed using thematic charts. Multiple strategies, including peer debriefing, will be implemented to address potential investigator bias and enhance the study’s credibility. Maintaining comprehensive documentation will also ensure that an audit trail is available for future reference.

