## Results

The study was funded in January 2021. Data collection started in May 2021 and ended in mid-2022. In total, 103 dyads were matched at the beginning of the intervention. Of the 103 dyads, 90 (87.4%) dyads completed the midtest survey and 64 (62.1%) dyads completed the posttest survey. Although a total of 92 dyads were planned to test the effectiveness of the intervention in this proposed study, the post hoc power analyses performed using G*Power 3.1.9 indicated that 64 dyads will yield sufficient power to test the interaction between groups over time (power=0.95), the changes over time (power=0.95), and the differences between the groups (power=0.71). These parameters are based on a small anticipated effect size (*f*=0.22), α=0.05, two-tailed, with measures correlated at r=0.30.

We also collected qualitative interview data for this study with selected dyads in the intervention group (8/27, 30%). Weekly reflection page from UTA student participants, weekly fidelity check forms, final digital story books, and final scrapbooks were also saved for future data analyses. We are currently engaged in data cleaning and analysis for both quantitative and qualitative data. One manuscript has already been published [73], and we anticipate publishing several more manuscripts reporting the results within the next 1-2 years.

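### Baseline is modelled as an ordinary outcome wave, and the follow-up to a significant interaction cannot show when, or by how much, the arms differ

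*Protocol article*

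**What the plan says.** All references are to the protocol article.

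- **Outcome vector (Statistical Analysis).** The covariate-adjusted linear mixed model takes as its outcome four scores: "the dependent variable will be the scores before the intervention, in the middle of the intervention, at the end of the intervention", and the 3-month follow-up.
- **Covariates.** The model's covariates are those that differ significantly between groups in univariate tests; the examples are age, sex, education, income and health conditions. Factors related to dropout (Data Collection Plan) and documented contamination (Procedure) may be added. The baseline value of the outcome is not named, and no constraint of equal baseline means is stated.
- **Between-arm estimates.** The same section says the models compare the arms over time and promises a 95% CI for each adjusted mean difference. It does not say which differences or which waves.
- **After a significant interaction.** "groups will be isolated, and patterns of change will be identified via linear mixed models for repeated measures (with no between-participants factors" is the only follow-up described.
- **Hypotheses.** Goals 1 and 2 ask for two things, in the middle of and after the intervention: change from pretest and difference from control. Goal 3 splits these. Its first hypothesis is within-arm (volunteers "will have more positive attitudes toward aging after the intervention compared with that before the intervention") and its second compares with control.
- **Power (Results).** At 64 dyads: 0.95 for the interaction, 0.95 for time and 0.71 between groups, with f=0.22 and "α=0.05, two-tailed, with measures correlated at r=0.30".

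**The concern.** Participants are randomised after baseline assessment, so the arms have the same expected score at the first wave. A group main effect over all four waves averages that zero with the later effects. If baseline is left as an unconstrained response, a contrast in change from baseline also carries the full noise of the baseline score instead of using it to reduce variance.

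The interaction test avoids the dilution, but it has three degrees of freedom and says only that the profiles differ somewhere. The described next step then removes the arm factor. Significant change in one arm and not in the other is not a test of the difference between them. Within-arm change can also come from time trends (data were collected during the pandemic) or regression to the mean. The comparison with control at each wave, which Goals 1 and 2 hypothesise, is therefore not the described output of that step. With posttest data on 64 of 103 dyads, there is little precision to spare.

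**Working it through.** **Inputs.** Effect: "This sample size estimate was based on a small effect size", f=0.22, which is d = 2f = 0.44 SD for two equal groups. Two-sided α=0.05. r=0.30 between waves. Allocation 1:1: "Half (46/92, 50%) of the dyad sample will receive the reminiscence DST intervention". N=64 dyads with posttest, 92 planned. Assumed here: compound symmetry, complete data, and the effect patterns named below.

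**1. The plan's own power.** For m waves the noncentrality is:
- between groups: λ = f²·N·m / (1+(m−1)r), df 1 and N−2
- interaction: λ = f²·N·m / (1−r), df m−1 and (N−2)(m−1)

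With m=4:
- between: 0.0484×64×4/1.9 = 6.52, power 0.710
- interaction: 0.0484×64×4/0.7 = 17.70, power 0.952

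With m=3:
- between: 0.0484×64×3/1.6 = 5.81, power 0.660
- interaction: 0.0484×64×3/0.7 = 13.28, power 0.907

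The stated 0.71 and 0.95 match four waves, so baseline is counted. The planned 92 fits less cleanly. Three waves need 89 (94 after 5% attrition) and four need 79 (84 after attrition). The evidence on baseline is therefore the model description and the Results power, not the planned sample size.

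**2. Dilution of the group main effect.** With arm differences (0, 0.44, 0.44, 0.44), the four-wave mean is 3×0.44/4 = 0.33, so f = 0.165. Then λ = 0.165²×64×4/1.9 = 3.67 and power is 0.47 (0.62 at 92 dyads).

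**3. Interaction under the same pattern.** f = √(3/16)×0.44/2 = 0.095. Then λ = 0.095²×64×4/0.7 ≈ 3.32 on 3 and 186 df, and power is 0.30. The stated 0.95 takes f=0.22 for the interaction itself, which is a different and much larger pattern of effect.

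**4. Baseline-adjusted average of the three later waves.** Variance factor (1+2r)/3 − r² = 0.533 − 0.09 = 0.443. Then λ = 0.44²×64/(4×0.443) = 6.99 and power is 0.74 (0.88 at 92).

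**5. One later wave.** In units of σ², the variance is 2(1−r) for change from baseline and 1−r² when baseline-adjusted. At r=0.30 these are 1.40 and 0.91. The ratio is 2/(1+r): 1.54 at r=0.30, 1.33 at r=0.5, 1.18 at r=0.7. For d=0.44 at 64 dyads, power is 0.31 against 0.44. If the promised CIs are instead plain differences at a wave, the ratio is 1/(1−r²) = 1/0.91 = 1.10 at r=0.30; the article does not say which is meant.

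**6. Other effect patterns, N=64, r=0.30.**

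| Pattern | Four-wave main effect | 3-df interaction | Baseline-adjusted average |
|---|---|---|---|
| Constant 0.44 | 0.47 | 0.30 | 0.74 |
| Half at midpoint, then 0.44 | 0.35 | 0.27 | 0.58 |
| None until end, then 0.44 | 0.24 | 0.39 | 0.41 |

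If the effect is at the end only, or at 3 months only, the interaction has 0.30 and the average 0.14. If there is no effect until the end, the interaction beats the average at r=0.5 (0.52 v 0.43) and at r=0.7 (0.77 v 0.55).

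**The case against.** A reader might infer that the plan abandons the randomised comparison. It does not. The group-by-time interaction compares randomised arms, and 95% CIs for adjusted mean differences are promised. The separate-arm models come only after a significant interaction, and they serve the stated change-from-pretest hypotheses; Goal 3 pairs its within-arm hypothesis with a controlled one. What remains is that this follow-up step contains no between-arm contrast, and the waves covered by the promised CIs are not named.

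A reader might also infer that keeping baseline as a response wastes power in itself. It need not: a four-wave model with baseline means constrained equal is about as efficient as baseline adjustment. The loss belongs to the ordinary unconstrained model. The article's wording suggests that model without stating it, and a fuller analysis plan might specify otherwise. The article does, however, fix the outcome vector, the covariate rule and the follow-up step.

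Nor do the figures justify replacing the interaction with a single averaged contrast. Digital storytelling occupies weeks 7 to 10, so a late effect is plausible, and there the average can lose to the interaction. The 0.74 belongs to the most favourable of the tabulated patterns.

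Finally, 64 complete dyads understates the information available. Likelihood-based models also use partial records, and 90 dyads had a midpoint survey. The absolute powers are therefore not those of the planned analysis, but 64 is the number the article itself uses.

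**Conclusion.** The point holds in a limited form. Baseline is one of four outcome waves with no stated baseline adjustment or constraint, and the reported 0.71 assumes that the effect is spread over all four. For a constant later effect of 0.44 SD, the four-wave group effect has power 0.47 at 64 complete dyads. A single-wave change contrast has 1.54 times the variance of a baseline-adjusted one, falling to 1.18 at r=0.7. Separately, the arm-by-arm follow-up cannot show at which wave, or by how much, the arms differ. These sizes rest on compound symmetry, complete data, the article's r=0.30 and the assumed effect patterns; the dilution by a quarter rests only on randomisation and a constant later effect. The trial still has a valid randomised test. What is lost is precision and a direct answer to the comparison-with-control hypotheses.

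**What to change.** For each outcome:

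1. Fit one joint mixed model, either with midpoint, end and 3-month scores as responses and the baseline score as a covariate, or with all four waves and baseline means constrained equal across arms. State which.
2. As the follow-up to the interaction, report between-arm contrasts with 95% CIs at midpoint, end and 3 months from that model, and make clear that these are the adjusted mean differences promised.
3. Keep within-arm change as description only, and base no claim of effect on it.
4. An average over the later waves may be added, but should not be the sole test.

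No new data are needed, because baseline scores are already collected. The gain is modest for a single wave: adjusted power there is still 0.44 at 64 dyads under the assumptions above. The cost is procedural. Data collection has ended, preliminary results are described and one manuscript is published. The change should therefore be a dated amendment that says it was made after data collection and identifies any outcome already analysed.

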### Data Management and Participants’ Safety

The research team will be the sole individuals with knowledge about and access to the names of both the older and young participants. Although certain demographic information, such as age, sex, and racial and ethnic background, may be recorded, the questionnaires will not contain any participant identifiers such as date of birth or address. The preintervention and postintervention questionnaires will also be devoid of participant identifiers. To ensure confidentiality, participant names will be deidentified, with each individual assigned a unique study identifier or number. All data files will be securely stored in encrypted, password-protected folders on laptops provided by UTA. These laptops will also have encryption in accordance with the guidelines set by the UTA Office of Information Technology. Participant privacy will be diligently safeguarded, and records containing names and other identifiable information will be stored separately from the interviews, using password-protected, encrypted files on UTA-issued laptops. The PI (LX) and the UTA institutional review board (IRB) will bear the responsibility of ensuring participant safety and the attainment of the study’s scientific objectives. The research team possesses previous experience in organizing and managing clinical trials, including implementing data safety monitoring measures for interventions.

All the older adults and young adult volunteers will provide informed consent before participating in the study. Potential participants will be informed that refusal to consent to the study or withdrawing from the study will have no effect on the services that they currently receive or might receive through UTA (ie, young adult volunteers) or through MOW or the Area Agency on Aging (ie, older adults). Participants who provide informed consent will be contacted for baseline measurement and then randomized to 1 of the 2 treatment groups. The protocol and consent forms will be approved by the UTA IRB before conducting any study procedures. Student members of the research team will receive training regarding procedures required to obtain informed consent.

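### The pre-randomisation score is modelled as a fourth outcome with no baseline adjustment or common baseline mean, so the two between-arm tests the article names lose precision

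*Protocol article*

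**What the plan says.** The Statistical Analysis section of the protocol article specifies covariate-adjusted linear mixed models for repeated measures, in which "the dependent variable will be the scores before the intervention, in the middle of the intervention, at the end of the intervention"; the fourth score listed is the 3-month one. On adjusters it says: "The covariate will be any significant variable yielded from the univariate analyses". The variables to be screened are participant characteristics "such as age, sex, education level, income, and health conditions". Elsewhere, the Procedure section adds documented contamination as a covariate, and the Data Collection Plan adds factors related to dropout. No section names the baseline score of the analysed scale as an adjuster, and none says that the arms share a baseline mean.

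Under Data Management and Participants’ Safety, participants are "contacted for baseline measurement and then randomized to 1 of the 2 treatment groups", so baseline precedes allocation. Differing patterns of change are to be "identified via a significant interaction in linear mixed models". The Results section gives post hoc power at 64 dyads of 0.95 for the interaction, 0.95 for change over time and 0.71 for the difference between groups, "with measures correlated at r=0.30". The Sampling and Recruitment Plan uses the same correlation and f=0.22.

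**The concern.** Randomisation makes the arms' baseline means equal in expectation. A model that gives each arm its own baseline mean does not use that fact. Its interaction contrast is then a difference in change from baseline, which at a low correlation is noisier than ignoring baseline. Its group effect averages four scores, one of which cannot show a treatment effect.

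The between-group test has the lowest stated power (0.71). Only 64 of 103 matched dyads completed the posttest, against 92 planned. The lost sample cannot be recovered, but the information in the baseline survey has already been collected. The same section declines a multiplicity adjustment because of the risk of type 2 error, so power is a concern the authors state themselves.

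**Working it through.** **Inputs.** From the article: r=0.30, f=0.22 (d = 2f = 0.44 for two equal groups), two-sided α=0.05, 64 dyads, four measurements. Assumed here: 32 dyads per arm, equal SDs (set to 1), one correlation at all lags, complete data, and an effect absent at baseline and constant at the three post visits.

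**The article's own figures, for N=64.** N·f²·m = 64 × 0.0484 × 4 = 12.39.
- Between groups: λ = 12.39/(1 + 3×0.30) = 6.52 on (1, 62) df, power 0.710 (stated 0.71).
- Interaction: λ = 12.39/(1 − 0.30) = 17.70 on (3, 186) df, power 0.952 (stated 0.95).
- With three measurements the values would be 0.66 and 0.91. The stated power therefore counts four scores, which fits baseline being one of the outcomes.

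**Variance per arm at r=0.30, in units of SD²/n.**

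| Contrast | Change from baseline | Raw post score | Baseline-adjusted | Change / adjusted | Raw / adjusted |
|---|---|---|---|---|---|
| One visit | 2(1−r) = 1.40 | 1.00 | 1−r² = 0.91 | 1.54 | 1.10 |
| Mean of three post visits | (1+2r)/3 + 1 − 2r = 0.933 | (1+2r)/3 = 0.533 | 0.533 − r² = 0.443 | 2.11 | 1.20 |

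The four-score group effect has variance (1+3r)/4 = 0.475 but picks up only 3/4 of the post-visit effect. Rescaled, this is 0.475/0.75² = 0.844, and 0.844/0.443 = 1.90.

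A generalised least squares calculation with 46 per arm gives the same 1.54 and 2.11 when free baseline means are compared with one common baseline mean. The constrained model therefore recovers the full gain of adjustment.

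**Power on matching contrasts, 32 per arm, d=0.44.** The 1-df tests use a noncentral t with 62 df and noncentrality 0.44/√(2v/32), where v is the variance above.
- Three-visit mean: change 1.82, power 0.43; adjusted 2.64, power 0.74. Raw gives 2.41, power 0.66.
- One visit: change 1.49, power 0.31; adjusted 1.84, power 0.44. Raw gives 1.76, power 0.41.
- Four-score group effect: 1.92, power 0.47.

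The 3-df joint test uses a noncentral F on (3, 186) df, with 16 × 0.44² = 3.098.
- Change: covariance 1.40 on the diagonal and 0.70 off it, so λ = 3.098 × 3/(1.40 + 2×0.70) = 3.32, power 0.30.
- Adjusted: 0.91 and 0.21, so λ = 3.098 × 3/(0.91 + 2×0.21) = 6.99, power 0.58.

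**Why 0.71 and 0.47 differ.** The stated 0.71 applies f=0.22 to the average of all four scores, baseline included. If the effect exists only after baseline, the same test has power of about 0.47.

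**The case against.** The strongest defence is that keeping baseline among the repeated outcomes is a valid, widely used model. It is unbiased under randomisation and has the right type I error, and the authors call the study preliminary. This stands.

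Second, the article does not say which contrast is the treatment effect. It promises 95% CIs for adjusted mean differences, which can be read as between-arm differences at each wave. On that reading the penalty is only 1.10 to 1.20. This also stands and bounds the claim from below. The tests the article names and powers, though, are the two costly ones.

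Third, separate baseline means are an inference, because no parameterisation is given and a constraint could sit in an analysis plan that is not shown. That is possible. What the article does fix is the list of outcomes and the rule for covariates, and neither uses the baseline score. If the score passed the open-ended significance screen, it would be outcome and covariate at once.

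Fourth, 32 per arm is an assumption. The 8/27 given for interviewed intervention dyads hints at unequal arms. With 27 and 37, 1/27 + 1/37 = 0.0641 against 2/32 = 0.0625, about 2.5% more variance for every method, so the ratios do not change. The 90 dyads with midtest data would add information that these complete-data figures ignore.

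A reader might also set the interaction's 0.30 against the adjusted three-visit mean's 0.74 and credit the whole gap to baseline adjustment. That compares a 3-df test with a 1-df test; like for like, the pairs are 0.30 and 0.58, and 0.43 and 0.74.

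**Conclusion.** The concern holds as a loss of efficiency. For the between-arm tests the article names, the variance is about 1.5 times that of a baseline-adjusted estimate at one visit and 1.9 to 2.1 times averaged over the post visits. It is 1.1 to 1.2 times if raw post-visit differences are read from the same model. These ratios rest on r=0.30 at all lags, equal variances and complete data; the power figures also rest on 32 per arm and a sustained d=0.44.

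A reader might infer that the planned analysis is invalid or biased, or that the variance is doubled whichever contrast is reported. The documents support neither: allocation follows baseline, so the contrasts are unbiased, and the doubling belongs to particular contrasts that the article does not single out as the treatment effect. This should be fixed, but the trial's validity does not depend on it.

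**What to change.** In the Statistical Analysis section, keep all four scores in the outcome vector, constrain both arms to one common baseline mean, and let the arms differ freely at midpoint, end and 3 months. Report the between-arm difference with 95% CI at each post visit and averaged over the post visits.

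This form is preferable to moving baseline out of the outcome and into the covariates. Goals 1 to 4 state hypotheses against participants' own pretest or pre-intervention scores, and a model with only post scores as outcomes would lose those contrasts. The constrained model keeps them. It also retains dyads with no later score; 13 of the 103 (103 − 90) had no midtest.

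The cost is small: no new data, one paragraph of wording and a different model specification. It is not free, because data collection has ended and the abstract reports preliminary results. The change has to be disclosed as made after the original plan, and showing the originally specified model beside it would let readers judge its influence.

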#### Goal 1—To Quantitatively Test the Effectiveness of This Intervention in Improving the Social Well-Being of Older Adults With ADRD and Young Adults

The objectives are to (1) provide a 10-session intervention with reminiscence and DST to older adults by trained young adult volunteers and (2) test whether older or young adults report significant improvement in quality of life or decline in loneliness after the intervention. Hypotheses include the following: (1) older participants in the intervention group will have high levels of quality of life in the middle of and after the intervention compared with their pretest scores and compared with those in the control group and (2) young and older participants in the intervention group will have low levels of loneliness in the middle of and after the intervention compared with their pretest scores and compared with those in the control group.

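### After a significant group-by-time interaction the only follow-up test named is within-arm, so that step gives no estimate or test of the arm difference at any survey

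*Protocol article*

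**What the plan says.** The hypotheses under Goal 1 are both within-arm and between-arm: intervention participants are to do better "in the middle of and after the intervention compared with their pretest scores and compared with those in the control group". Goal 2 has the same structure for affect and resilience. Goals 3 and 4 add arm comparisons after the intervention for the young adults.

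Under Statistical Analysis the main analysis is two-arm: "Covariate-adjusted linear mixed models for repeated measures will be performed to compare the intervention and control groups over time". The dependent variable is "the scores before the intervention, in the middle of the intervention, at the end of the intervention, and at 3-month follow-up", so there are four time points. The section adds that "95% CIs will be computed for each adjusted mean difference", without saying whether these are differences between arms or between time points, or at which survey.

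The section then takes the case where one group's pattern over time is not seen in another. That case "would be identified via a significant interaction in linear mixed models, would require post hoc testing to investigate the nature of changes over time". The only post hoc test it names is the one in which "groups will be isolated, and patterns of change will be identified via linear mixed models for repeated measures (with no between-participants factors".

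**The concern.** The between-arm hypotheses are about particular times. A colleague who sees a significant interaction will next ask which arm did better, at which survey, and by how much. The named follow-up removes the group factor, so it answers a different question: whether each arm, on its own, changed over time. That leaves the reader to compare a p-value from one arm with a p-value from the other, which is not a test of the difference between arms.

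At stake is the interpretation of the primary outcomes: quality of life, loneliness, affect and resilience in the older adults. Without arm contrasts, a positive interaction could be reported with no effect size for the randomised comparison, or attributed to the wrong survey.

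**Working it through.** **1. The plan's own interaction figure.** The Results section gives post hoc power with 64 dyads of 0.95 (interaction), 0.95 (time) and 0.71 (groups), for f = 0.22, r = 0.30 and α = .05. With m = 4 surveys:
- Interaction and time: λ = N f² m/(1 − r) = 64 × 0.0484 × 4/0.70 = 17.70 on (3, 186) df; power 0.952.
- Groups: λ = N f² m/(1 + (m − 1)r) = 12.39/1.90 = 6.52 on (1, 62) df; power 0.710.

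All three reproduce with four surveys, so the interaction has 3 df.

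**2. What that interaction cannot tell.** Take 32 dyads per arm (an assumed even split of 64) and an arm difference of 0.6 SD. Then λ = (32 × 32/64) × S/(1 − r), where S is the sum of squared deviations of the four arm differences from their mean.

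| Arm difference at the four surveys | S | λ |
|---|---|---|
| 0, 0.6, 0.6, 0.6 (benefit throughout) | 0.45² + 3 × 0.15² = 0.27 | 16 × 0.27/0.70 = 6.17 |
| 0, 0.6, 0, 0 (benefit at midpoint only) | 3 × 0.15² + 0.45² = 0.27 | 6.17 |
| 0, −0.6, −0.6, −0.6 (harm throughout) | 0.27 | 6.17 |

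The three situations have the same noncentrality. The F test cannot separate them, so the next step has to.

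**3. How the named next step behaves.** Simulation with r = 0.30, four surveys, 32 per arm and a 0.6 SD arm difference at all three later surveys (the 0.6 is assumed). The two-arm interaction is tested first, then a time effect in each arm separately, all at .05.
- Difference split +0.3/−0.3: the interaction is significant in 52% of trials. Among those, the intervention-arm model is non-significant in 0.287/0.520 = 55%. At least one arm's model is significant in about 76%, so neither is in 24% to 25%.
- In interaction-positive trials under the same assumptions, at least one of the three between-arm change-from-baseline contrasts (unadjusted) significantly favours intervention in over 99%.

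**4. Comparing two within-arm results at one survey.** Suppose both arms truly improve by the same 0.4 SD. The change score has variance 2(1 − 0.30) = 1.4. With 46 per arm, the power in each arm is Φ(0.4/√(1.4/46) − 1.96) = 0.630. Exactly one arm is then significant with probability 2 × 0.630 × 0.370 = 0.47, although the arms do not differ.

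Now restrict to trials with a significant interaction. Let the arms differ by 0.6 SD at midpoint only and both improve by 0.4 SD at the end (46 per arm). The interaction is significant in 69% of trials. Among those, the pattern of intervention significant and control not significant at end of intervention appears in 26%. A direct arm contrast at that survey favours intervention in 3%.

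**The case against.** The strongest reply is that the randomised comparison has already been made. The two-arm model comes first, and the interaction that triggers the follow-up is itself a comparison of the randomised arms. The follow-up is described as looking into changes over time, and change from pretest is a stated hypothesis that within-arm models do address. The promised intervals for adjusted mean differences come directly after the two-arm model and may well be arm differences by survey. All of this stands. A reader might infer that the plan discards the randomised comparison, or cannot show at all that the arms differ; the text does not support that.

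A reader might also infer that the within-arm step hides a benefit when controls decline and the intervention arm holds steady. That does not follow either. The intervention arm then has no true change, so a non-significant result there is correct. The control-arm model, which is also run, is significant in about 97% of interaction-positive trials under the step 3 assumptions. If instead the whole 0.6 SD is improvement in the intervention arm, which is the pattern the trial hypothesises, that arm's model is significant in about 97% of them.

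What the reply does not supply is an arm contrast at a named survey. The interval sentence leaves the type of difference open, and the only post hoc test actually named is within-arm. Because that test is a stated choice, it is more than detail left to an unseen analysis plan.

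**Conclusion.** The point holds as a defect in the follow-up step. The plan can show that trajectories differ, but its named next step gives no estimate, interval or test of the arm difference at midpoint, end of intervention or 3 months, and Goals 1 and 2 need that.

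The size depends on how the effect arises. If the arms move in opposite directions (+0.3/−0.3 SD), neither within-arm model is significant in about a quarter of interaction-positive trials. If the whole effect lies in one arm, that arm's model usually detects it, but there is still no estimate of the difference. The 0.6 SD effect and the even 32/32 split are assumptions; r = 0.30 and the total of 64 dyads are the article's. The Results section mentions 27 intervention dyads, which would mean 27/37 if the 64 completers are the base. No sample-size figure depends on this point.

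**What to change.** Replace the sentence on isolating the groups with: *A significant interaction will be followed by arm-versus-arm contrasts with 95% CIs at midpoint, end of intervention and 3 months, estimated from the full two-arm mixed model.* State that these contrasts are the adjusted mean differences for which intervals are promised. Keep the within-arm models as descriptive support for the comparisons with pretest.

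The cost is one or two sentences. SPSS gives the contrasts as estimated marginal means compared by group at each survey, from the model already planned. No new data are needed. The Results section says analysis is still under way but that one manuscript is already published, so the change should be dated and reported as made after data collection ended.

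The contrasts should be read as estimates with intervals, because single-survey power is modest. Taking d = 2f = 0.44 and r = 0.30 (normal approximation), power is Φ(0.44/(σ√(2/n)) − 1.96), with σ = √(1 − 0.09) if baseline-adjusted and σ = √1.4 for change scores. That gives 0.60 and 0.43 with 46 per arm, and 0.45 and 0.32 with 32 per arm.
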